## Abstract

**Background:**

Maintaining independence is of key importance to older people. Ways to enable health strategies, strengthen and support whanāu (family) at the community level are needed. The Ageing Well through Eating, Sleeping, Socialising and Mobility (AWESSOM) programme in Aotearoa/New Zealand (NZ) delivers five integrated studies across different ethnicities and ages to optimise well-being and to reverse the trajectory of functional decline and dependence associated with ageing.

**Methods:**

Well-being, independence and the trajectory of dependence are constructs viewed differently according to ethnicity, age, and socio-cultural circumstance. For each AWESSoM study these constructs are defined and guide study development through collaboration with a wide range of stakeholders, and with reference to current evidence. The Compression of Functional Decline model (CFD) underpins aspects of the programme. Interventions vary to optimise engagement and include a co-developed whānau (family) centred initiative (Ngā Pou o Rongo), the use of a novel LifeCurve™App to support behavioural change, development of health and social initiatives to support Pacific elders, and the use of a comprehensive oral health and cognitive stimulation programme for cohorts in aged residential care. Running parallel to these interventions is analysis of large data sets from primary care providers and national health databases to understand complex multi-morbidities and identify those at risk of adverse outcomes. Themes or target areas of sleep, physical activity, oral health, and social connectedness complement social capital and community integration in a balanced programme involving older people across the ability spectrum.

**Discussion:**

AWESSoM delivers a programme of bespoke yet integrated studies. Outcomes and process analysis from this research will inform about novel approaches to implement relevant, socio-cultural interventions to optimise well-being and health, and to reverse the trajectory of decline experienced with age.

**Trial registration:**

The At-risk cohort study was registered by the Australian New Zealand Clinical Trials registry on 08/12/2021 (Registration number ACTRN 12621001679875).

## Background

Those aged over 75 years will make up 12.5% (currently 5%) of the New Zealand (NZ) population by 2051, and it is estimated that the proportion over age 85 years will quadruple over the next 20 years. Diversity of the ageing population is also increasing. The majority Pakeha (European) population aged 65 and over will fall in proportions from 88 to 75% from 2013 to 2038 with increases for Asian (5to 16%), Māori (6 to 10%) and Pacific people (2 to 4%) [1, 2]*.* Associated with this is an increase in age-related burden, manifesting as functional decline and attenuated quality of life. Understanding the cause of functional decline and age-related burden is challenging, and although progress has been made the evidence for mitigating risk factors is inconsistent [3, 4]. The need for improved outcomes through many pathways is emphasised, and specific strategies for Māori and Pacific peoples in NZ have been developed. The Ageing Well through Eating, Sleeping, Socialising and Mobility (AWESSoM) programme has two broad aims: firstly to enhance knowledge of risk factors for functional decline especially for populations with scant extant data, and secondly to improve function, health and well-being in older adults. It does so via an inclusive research protocol, drawing on the essential nature of community development, Kaupapa Māori approaches to health, consideration of strengthening of social capital, and broadening of primary health care. The AWESSoM programme delivers five studies that subscribe to an interconnected understanding of function, health and well-being: 1) Māori health and well-being; 2) Pacific elders health and well-being; 3) older community dwellers at risk of functional decline; 4) complex multi-morbidity analyses, and 5) aged residential care. Common themes or target areas for investigation connect these studies and include *sleep, physical activity and mobility, oral health,* and *social connectedness.* These themes are explicitly investigated throughout the programme in all sector groups to a greater or lesser degree, as discussed below (Fig. 1).

**Fig. 1 Fig1:**
[figure not shown]
Visual presentation of integrated AWESSoM themes: function & well-being in different populations specifically examining oral health, sleep health, social connection, and physical activity patterns. COMPASS, COMPASS Health (Primary Health Organisation); interRAI, International Residential Assessment

### AWESSoM: Māori health & well-being (Nga Pou o Rongo)

Growth in the population of older Māori (indigenous people of Aotearoa/New Zealand) is predicted to be double that expected for non-Māori. Social, economic and environmental factors impact health and political, cultural and historical factors add to these as recognised factors related to health disparities for Māori in NZ. Older Māori are more likely to experience disadvantage and hardship at a level which is three-to-four times that of non-Māori. Higher levels of complex co-morbidities, disability yield differences in longevity between Māori and non-Māori of 8.6 and 7.9 years for men and women respectively [2]. Māori share robust whānau networks; a collective societal responsibility and whakawhānaungatanga (process of establishing relationships, relating well to others). The rate of admission to residential care (termed care homes in this proposal) is lower for Māori than non-Māori [5] and as a result Māori with high levels of disability are cared for at home [2]. Clusters of conditions for Māori differ from those for non-Māori [6] suggesting that ethnic-specific understandings of disease processes are needed.

### AWESSoM: Pacific elders health & well-being (Pacific elders)

Seven percent of NZers identify with at least one Pacific ethnic group, an increase of 11% since 2006 [1]*.* In particular, the Pacific population aged 65 plus is increasing faster than non-Pacific people, and health outcomes for Pacific peoples lag behind those of non-Pacific people in all domains of health [7]. The Healthy Pacific Grandparents (HPG) Study, a participatory action research project developed in collaboration with elder members of Vaka Tautua, a ‘by Pacific for Pacific’ health and social service provider [2] investigated whether the current social and health system environments meet Pacific elders’ needs. Key findings included a recognition by Pacific elders of the importance of taking responsibility for one’s own health and wellbeing but also identified key issues limiting optimal health and well-being and the barriers Pacific elders face in overcoming these. The HPG study also identified a role for technology to enable communication, provide entertainment and leisure options, however limited expertise and lack of exposure impacted on uptake.

### AWESSoM: improving functional decline in older community dwellers (at-risk cohort)

The first target area to be examined in the At-risk cohort is *oral health*, which is a largely unrecognized but major health issue. Demographic and oral epidemiological changes (and associated health issues) among older NZers present an unprecedented situation: poor oral health is considered one of the ‘geriatric giants’ [8]*.* Dental caries remains the major oral health problem in older age, exacerbated by multimorbidity and associated polypharmacy which can compromise saliva flow, leading to higher rates of dental caries, along with problems eating, chewing, speaking and swallowing [9, 10]*.* The second target area is *sleep****,*** which is a problem for over a quarter of older adults [11]. Sleep disturbances are bidirectional, acting both as a precursor to and exacerbating comorbid diseases. For example, sleep disturbances are strongly associated with cardiovascular disease [12]*,* and mental and neurological problems (e.g. depression and/or cognitive impairment), as well as external factors such as social isolation and grief [13]*.* The third area relates to *function*, which manifests as the ability to perform activities of daily living (ADL) [14] in home and community settings (community ADLs are instrumental or extended activities of daily living: IADLs) [15]*.* ADLs and IADLs attenuate in a certain order and operate in a hierarchy of functional domains, described by the Lifecurve hierarchy (see Fig. 2) [17]. The fourth focus area is *physical activity and mobility.* Epidemiological evidence that habitual activity benefits longevity, cardiovascular health and well-being for older people is overwhelming, and this is no less apparent in NZ [18]. Physical activity (or exercise) improves functional status, sleep, health status and life satisfaction for older people [19] and is effective in the treatment of cardiovascular disease, diabetes mellitus, falls and cognitive decline. Despite this, levels of physical activity remain low in older people, and behavioural change strategies are challenging to implement; this is even more so for people with compromised mobility. The final targeted area for the At-risk community cohort is *socialisation.* It is clear that social participation and social support networks are key to long-term outcomes and psychological wellbeing [20]*.* While the exact mechanisms by which social ties and contacts influence psychological morbidity is debated [21], it is clear that social issues contribute to depression and loneliness [22].

**Fig. 2 Fig2:**
[figure not shown]
LifeCurve™ hierarchy of functional decline *(reprinted with permission)* [16]

### AWESSoM: aged residential care (care home)

Accommodation and health care is provided for our most vulnerable population in aged residential care facilities, termed “care homes” which include rest home, hospital-level and dementia-level care for older people in NZ. Over 60% of NZ and Australian care home residents have memory problems [23] or dementia. AWESSoM takes advantage of NZ’s universal comprehensive geriatric assessment (the international Residential Assessment Instrument, interRAI) [24] to enable identification of individuals with aspects of health relevant to this study, particularly in respect to oral health, sleep, and cognitive decline. Oral health in residential care is a particularly vexing issue, with neither the care sector nor the dental profession prepared for the steadily increasing number of residents entering care with disproportionately high levels of tooth decay, their own teeth, and accompanying risk of aspiration pneumonia [25]*.* Similarly, sleep has been identified as a complex issue within care homes. This is due to an increase of sleep disorders with ageing and cognitive impairment alongside the impact of living and sleeping in a different environment with different schedules and exposures [26]*.*

### AWESSoM: multimorbidity

Multimorbidity may be defined as the presence of two or more chronic conditions with equal predominance [27, 28]*.* Prevalence of multimorbidity is high in older adults, resulting in poor outcomes, polypharmacy [29] and uncertainty about management. People with multimorbidity are 3.5 times more likely to have problems with ADLs and 6 times more likely to have physical function limitations than those without after adjusting for socioeconomic status and depression [30]. Health care costs are 2.5 times higher for those with multimorbidity than for people with a single disease [4]. Guidelines call for individualised treatment, but empirical evidence identifies a lack of understanding of what constitutes individualised care [28]. Patterns of conditions (clusters) may be more relevant for identifying key areas of need and outcomes than a simple count of the number of conditions an individual has [6]*.* For example, cardiovascular clusters lead to the greatest decline in ADLs, while mental health/neurological clusters lead to a decline in IADLs [31]. Inconsistency in the choice of diseases included in studies and statistical methods provides challenges in describing patterns of multimorbidity.

## Methods/design

### Theoretical framework and study design

Models of health, well-being and functional independence underpin the AWESSoM programme. These models vary according to ethnicity, socio-cultural practice, and health/functional status but in essence all lead to an understanding about predictors of functional decline and strategies to mitigate it. Three of the five studies (Māori, At-risk cohort and Care Home studies) trial an intervention. For the Māori study researchers adapted previously trialled participatory action research techniques to develop and refine the intervention [32]. Co-design principles including group discussions, interviews and personal testimonies foster culturally safe practice and demonstrate cultural competence. This practice conforms to Mātauranga Māori - a cultural system of knowledge that reflects a unique Māori worldview. Pacific elders’ data are gathered via individual face-to-face interviews incorporating closed and open-ended questions, and focus group talanoa (conversations) to share views and arrive at common aims and understandings. The compression of functional decline model (CFD) model guides the At-risk study design. The CFD poses that decline in activities of daily living (ADLs) and instrumented activity of daily living (IADLS) is best compressed into the shortest possible time in order to extend the health span and thereby optimize ageing [33]. Decline in ADLs and IADLs occurs in a specific order, as described by the hierarchy of functional loss [17]. Longitudinal studies suggest the trajectory of loss can be reversed or at least remain static. The At-risk study examines this by trialling a novel intervention using a pre-post design. The Care Home and Multi-morbidity studies draw on the National Health Index (NHI) linked interRAI database contains data from standardised assessments of over 300,000 community-dwelling people and 200,000 residential care residents since 2012 with baseline and repeated assessments [24]. The assessment covers function, health conditions, aspects of oral health, nutrition, and mental health as well as indicators of sleep disturbance and function [34]. Finally the Multimorbidity studies also uses a second large extant datasets from primary health, the Compass Health Primary Care Organisation (PCO) dataset (Table 1).

**Table 1 Tab1:** AWESSoM studies: general characteristics

Study	Key concepts	Aims	Research Design	Outcomes
**Māori older adults** ***P*** Māori community dwelling older adults (age range 55+)	Exercise, nutrition, traditional well-being practices within Te Ao Māori, meditation, stress management, sleep, oral health	Modify and extend a family (whānau-based) lifestyle management strategy (Nga Pou o Rongo) Test scalability & acceptability of Nga Pou o Rongo Examine utility and potential value to Māori of ADL LifeCurve™ App	Conforms to Mātauranga Māori principles: whānau co-design, culturally safe & relevant, local, timely, affirmative, responsive to individual need)	Well-being, physical and social activity & health First in-depth sleep recordings of older Maori and consideration of sleep in contect of whānau support. Acceptability and usability of LifeCurve™ App
**Pacific elders** ***P*** Pacific elders (age range 55+)	Factors associated with ageing well	Investigate how Pacific elders are faring across various dimensions of health Examine utility and potential value of ADL LifeCurve™ App for Pacific elders	Collaborative design with Pacific community partner	Collection of data on Pacific health First representation of sleep health among Pacific elders
**At-risk cohort** ***P*** 300 Community dwelling older adults at risk of functional decline av. age 60 Māori, 75 non-Māori	Innovative technology, health promotion, behavioural change, hierarchy of function, trajectory of functional decline, independent & combined effect of physical activity, sedentary behaviour, socialisation and oral health on function, health & well-being	Adapt a behavioural change tool (LifeCurve™ App) to optimise locality in 2 urban sites Examine utility of and response to the ADL LifeCurve™ App on function, well-being and quality of life in 300 older adults living in the community. Evaluate use of LifeCurve™ App to reverse the trajectory of functional decline in participants Explore the interaction of physical activity, sedentary behaviour, socialisation and oral health on function and well-being.	Mixed methods design. Co-design to modify and develop LifeCurve™AppA for national and local content. Descriptive approach examines: 1) App acceptability, utility & engagment in health promotion activitites; and 2) associations and interactions of key components: physical activity, sedentary behaviour, socialisation, oral health. Pre-post design measures outcomes prior to introduction of LifeCurve™ App and at 12 m. Qualitatively, baseline and post-intervention semi-structured interviews with a diverse group of participants to seek views on App utility. Process evaluation (realist evaluation)	Interactions between sleep, oral health, physical activity, social connectedness, function, health & well-being Successful implementation of social connector model Effect of LifeCurve™ on function, health, well-being. Effect of LifeCurve™ on sleep, oral health, physical activity, social connectedness, function, health & well-being Clinically relevant change of ≥1 point on NEADL. Change ≥2 levels on the LifeCurve hierarchy of function
**Residential care** ***P*** Residents living in aged residential care	Novel interventions to improve oral health, cognition and sleep	Design and implement innovative strategies to improve oral health and cognition including introduction of a dental hygienst and cognitive stimulation theray programme.	Pre-post design with 3 month follow up	Changes in oral health, cognition, sleep and health status Estabishment of long term resources and programmes
**Multi-morbidity** ***P*** Community dwelling older adults, aged care residents (Age 55+; total popluation age 65+)	Patterns of multi-morbidity associated with functional decline and high burden of care.	Discern patterns of multi-morbidity associated with trajectory of dependence and high health services utilization Develop and refine primary care management based on most harmful patterns of multi-morbidity from primary care. Inform the design strategies for Care Home resident based on the most harmful patterns of multi-morbidity	Descriptive design. Multi-morbidity clusters modelled for each setting and for Māori, Pacific, & European using 2 extant data sources: Compass Health PHO and InterRai. Associations will be examined with hospital outcomes and burden of care.	Identify patterns of comorbidities of older adults living in New Zealand. Idenfity groups more likely to enter aged care facilities and others who are at an increased risk of mortality.

*Abbreviations: P* population, *NEADL* Nottingham Extended Activities of Daily Living scale, *PHO* Primary Health Organisation

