### Sample size calculation and data analysis

Estimates for sample size are considered formally for the At-risk cohort and the Multimorbidity study. The primary pre-post outcome for the At-risk cohort is functional status, measured by the Nottingham Extended Activities of Daily Living (NEADL). A power calculation based on data from a large longitudinal cohort examining health-status in older Māori and non-Māori (LiLACS NZ) indicated a sample size of 150 participants is required to show a pre-post change of at least 5 points on the NEADL scale which is considered a clinically significant change [46]. The Life Curve™ hierarchy over 12 months will be described for the cohort and patterns of change in response to the App will be modelled. Associations between NEADL, LifeCurve data, independent predictors of health and well-being, and data from oral health, social connectedness, physical activity and sleep will be examined. Objective sleep monitoring will take place for participants with self-identified sleep problems from the Nga Pou o Rongo, At Risk, and Care Home studies wearing the Motionlogger actigraph (Ambulatory Monitoring) (http://www.ambulatory-monitoring.com/motionlogger.html) a small wrist-watch-like device containing an accelerometer for 7 days. Standard sleep variables will be calculated (e.g. sleep timing, efficiency, and duration) as well as non-parametric circadian rhythm variables (inter-daily stability, and intra-daily variability) which are valuable for documenting regulation of sleep. This data will be used alongside subjective measures of sleep and physical and mental health status to better understand the predictors and outcomes of sleep disturbances across the studies and the effect of the App on sleep patterns. Data on App usage (e.g. number of times accessed, duration of use, functions accessed, tasks and activities selected and patterns of use, when and where) will also be evaluated. Information Power [54] will be used to determine sample sufficiency for the qualitative component. Qualitative data will be analysed drawing on reflexive thematic analysis [55]. Data from each time point will be analysed independently before being synthesised as a whole to produce standalone insights regarding the experiences and perspectives of the App and engagement in well-being strategies.

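### The single-group pre-post At-risk study cannot attribute 12-month change to the LifeCurve App or show that it reversed a trajectory, yet Table 1 states both

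*Protocol article*

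**What the plan says.** In the protocol article, Table 1 (At-risk cohort row) gives as one aim "Evaluate use of LifeCurve™ App to reverse the trajectory of functional decline in participants" and as one outcome "Effect of LifeCurve™ on function, health, well-being". A further outcome line words sleep, oral health, physical activity and social connectedness as App effects too.

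The design is set out under Theoretical framework and study design: "The At-risk study examines this by trialling a novel intervention using a pre-post design". Table 1 fixes the timing: "Pre-post design measures outcomes prior to introduction of LifeCurve™ App and at 12 m". No control group, run-in measurement or expected change without the App is described.

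Under Sample size calculation and data analysis, "The primary pre-post outcome for the At-risk cohort is functional status, measured by the Nottingham Extended Activities of Daily Living (NEADL"). The calculation, based on LiLACS NZ, "indicated a sample size of 150 participants is required to show a pre-post change of at least 5 points on the NEADL scale". Table 1 plans 300 participants.

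Three other statements bear on what may happen without the App:
- Entry requires one or two deficits that participants identify themselves on the LifeCurve (Setting, study population and recruitment).
- Other usual care continues (Data collection, assessment, intervention).
- The theoretical framework says: "Longitudinal studies suggest the trajectory of loss can be reversed or at least remain static".

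**The concern.** The aim and outcomes are causal, but the data will hold one before-and-after difference per person. That difference is the sum of any App effect and whatever would have happened anyway, and the design has nothing with which to separate them. A claim about a trajectory also needs either a slope before the App or an external expectation. Two time points give neither.

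The error can run both ways. In a cohort chosen as at risk of decline, stable function could be a benefit that a pre-post difference would not show. Conversely, drift, regression to the mean or usual care could produce a change that reads as an App effect. This matters beyond the paper, because Table 2 foresees long-term adoption of the App with health board support.

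**Working it through.** **Inputs from the article.** n = 150 and a change of 5 points (sample size section); 300 planned participants (Table 1). The article does not give the SD of change, alpha, sidedness, power, or the drift expected without the App.

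**The plan's own figure.** Without those inputs, 150 cannot be reproduced. It can be inverted. For a paired comparison, n = (SD × (z_alpha + z_power) / delta)². At two-sided 0.05 and 80% power:

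SD = 5 × √150 / (1.960 + 0.842) = 61.24 / 2.802 ≈ 21.9.

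The other usual choices give 18.9 (90% power, two-sided), 20.9 (90%, one-sided) and 24.6 (80%, one-sided). So the plan's figures imply an SD of change of roughly 19 to 25. An SD of 10 is kept below as a smaller alternative; for 5 points it would need only 32 participants at 80% power.

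**Chance of a significant result when the App does nothing.** Assume a background drift of m points and a two-sided 0.05 test of mean change against zero. With d = m × √n / SD, the normal approximation is

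P = 1 − Φ(1.96 − d) + Φ(−1.96 − d).

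Example: n = 150, SD = 21.86, m = 1. Then d = 12.247 / 21.86 = 0.560, and P = 0.081 + 0.006 = 0.087. The paired t-test gives 0.086.

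Paired t-test results:

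| SD of change | n | drift 1 point | drift 2 points |
|---|---|---|---|
| about 21.9 | 150 | 0.086 | 0.199 |
| about 21.9 | 300 | 0.124 | 0.351 |
| 10 | 150 | 0.229 | 0.682 |
| 10 | 300 | 0.408 | 0.932 |

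By symmetry, the same figures apply to a drift of −1 or −2 points, where the test would declare a decline. The rate rises with n, so going from 150 to 300 participants makes a wrong attribution more likely whenever the drift is not zero.

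**The opposite error.** If function would fall by m points without the App and the App prevents all of it, the mean change is −m + m = 0. A test against zero then rejects 5% of the time, whatever n is.

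**Sign of the drift.** The article does not fix it. Being at risk points to decline. Selection on self-reported deficits allows regression to the mean, but entry is a band of one or two deficits rather than an extreme, and the source-population mean is not given. Scores could regress in either direction. The selection is also on the LifeCurve, whereas the primary outcome is NEADL, which would weaken the effect.

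**The case against.** The strongest reply is that the design is deliberate and openly described: a real-world, mixed-methods, pre-post study with monitored App use and a realist process evaluation. The article is condensed, and reference values and models are often left to a full protocol or analysis plan. That is fair as far as it goes. But those elements do not supply the change without the App, and an analysis plan cannot add a control group or an earlier measurement. The causal wording is in the article's current text.

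Other parts of the reply stand and limit the point:
- A reader might infer that the plan tests change against zero. The article names no test or null value. It speaks only of showing a pre-post change, so zero is an assumption in the table above.
- A reader might infer that some recovery is to be expected and that the bias favours the App. The statement that loss can be reversed or stay static does not say that this happens without intervention, and the entry criterion does not fix a direction.
- A reader might infer that LiLACS NZ can supply the expected change. The article says only "A power calculation based on data from a large longitudinal cohort examining health-status in older Māori and non-Māori (LiLACS NZ"). It does not say that NEADL was measured about 12 months apart, that the entry ages and Pacific elders are covered, or that the team holds individual records.
- Significance is not the same as reaching 5 points. With 2 points of drift and n = 150, an observed mean of 5 or more occurs about 5% of the time at SD 21.9 (SE = 21.86 / √150 = 1.785; (5 − 2) / 1.785 = 1.68) and about 0.01% at SD 10.

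**Conclusion.** The point holds as a mismatch between claim and design. A single group measured twice can describe change over 12 months of App use. It cannot identify an App effect or a reversed trajectory, and that conclusion needs no numerical assumption.

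The size does need assumptions: drifts of 1–2 points, a two-sided 0.05 test against zero, and an SD of change that the article does not state. At the SD implied by the plan's own figures at 80% power, false attribution runs at about 9–20% (n = 150) or 12–35% (n = 300). At SD 10 it is 23–68% or 41–93%. Near-certain false attribution would require an SD well below the one that the sample size implies, so the documents do not support that stronger claim. Nor do they support saying that the bias runs in the App's favour, or that an external benchmark must become the primary contrast. Such a benchmark would replace one untestable assumption with another.

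**What to change.** - In Table 1, replace 'Effect of LifeCurve' in both outcome lines with 'change over 12 months of App use', and reword the aim of reversing the trajectory in the same way. Align the phrases in the sample size section that speak of response to the App and its effect on sleep.
- Report mean 12-month NEADL change with a 95% CI, and state that it is not attributed to the App.
- Check whether LiLACS NZ or another cohort has NEADL change over about 12 months in people of comparable age, ethnicity and baseline function. If so, add a prespecified secondary comparison with that expected change, described as non-concurrent and open to residual confounding. If not, make no claim of reversal.

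Recruitment and assessments are unchanged. The cost is some rewording, a more cautious conclusion and, if the comparison is added, a little extra analysis with lower precision. At equal SD, a reference change from m cohort members multiplies the standard error at n = 300 by √(1 + 300/m), which is 1.41 for m = 300 and 1.14 for m = 1000.

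### Two unreconciled clinically relevant thresholds, 1 point and 5 points, are given for the At-risk cohort's primary NEADL outcome, and the sample size supports only the 5-point one

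*Protocol article*

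**What the plan says.** All statements below are current text of the protocol article and concern the At-risk cohort.

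- **Table 1** (Theoretical framework and study design), Outcomes column: "Clinically relevant change of ≥1 point on NEADL". No reference, direction or level is attached. The next entry in the cell is a change of two or more levels on the LifeCurve hierarchy.
- **Sample size calculation and data analysis**: functional status on the NEADL is named as the primary pre-post outcome. The power calculation, based on data from an earlier longitudinal cohort, found that "a sample size of 150 participants is required to show a pre-post change of at least 5 points on the NEADL scale". The sentence goes on to call this change clinically significant and cites a source. It gives no direction, and does not say whether the 5 points is a mean or a per-person change.
- **Design**, Table 1: "Pre-post design measures outcomes prior to introduction of LifeCurve™ App and at 12 m". No comparison group is described.
- **Planned sample**, Table 1: "300 Community dwelling older adults at risk of functional decline".

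The article does not state the SD of change, alpha, sidedness, power or a dropout allowance.

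**The concern.** Cohort, instrument and 12-month interval are the same in both places, yet the change said to matter clinically differs fivefold. A mean change of 3 points, for example, is clinically relevant by Table 1 and below the clinically significant change in the sample-size section.

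This matters more than it would in a controlled trial. With no comparison group described, the reading of the main result leans heavily on whether the observed change is large enough to matter. If two published figures are available, the choice between them can be made after the results are seen.

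Direction adds to the ambiguity. The study aims to reverse functional decline, but both statements speak only of change, so neither says whether improvement alone is meant.

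**Working it through.** **Inputs from the documents:** n = 150 for a change of 5 points (Sample size calculation and data analysis); threshold of 1 point and planned sample of 300 (Table 1); single-group pre-post design.

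**Assumed, because not stated:** two-sided alpha 0.05, power 80% or 90%, no dropout, normal approximation for a paired mean change.

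**Step 1. The plan's own figure.** The formula is n = (SD × (z_alpha + z_power) / delta)². Without the SD, alpha and power, 150 can be neither confirmed nor refuted. Solving backwards for the SD of change gives SD = 5 × √150 / (z_alpha + z_power):

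- 80% power: 61.24 / 2.802 = 21.9 points
- 90% power: 61.24 / 3.242 = 18.9 points

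**Step 2. Size needed for 1 point.** With SD, alpha, sidedness and power held fixed, n is proportional to 1/delta². The ratio is (5/1)² = 25, so 25 × 150 = 3,750. The unstated inputs cancel. A t-based calculation at 80% power gives 3,698, hence about 3,700–3,750.

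**Step 3. Power for a 1-point mean change at the implied SD.** Power = Φ(√n / SD − 1.96):

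| n | SD 21.9 (80% design) | SD 18.9 (90% design) |
|---|---|---|
| 150 | 8% | 10% (0.095) |
| 300 | 12% | 15% |

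**Step 4. What 300 can detect.** At the same design power, the detectable mean change is 5 × √(150/300) = 3.5 points. That is below 5 but well above 1.

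**Step 5. Could 300 be enough for 1 point?** At 80% power the SD of change would have to be at most √300 / 2.802 = 6.2 (for n = 150, at most √150 / 2.802 = 4.4). At an SD of 6.2, however, 5 points would need only (6.2 × 2.802 / 5)² ≈ 12 participants, not 150. If 150 really is what 5 points requires, 300 cannot be enough for 1 point, because 300/150 = 2 and the ratio needed is 25.

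**The case against.** The best defence is that the figures sit at different levels. The 1-point entry stands beside the LifeCurve criterion, and a LifeCurve position belongs to an individual; the 5 points is the change used to size the cohort. An individual criterion and a group target may legitimately differ, and a responder definition is commonly left to the SAP, which is not shown. This is a possible reading, but the article does not state it. An SAP could choose between the figures, but it would not remove the conflict between two published statements. What stands is that the remedy may be a clarification and need not mean that one figure is wrong.

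Three stronger readings are tempting, and the documents do not support them.

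- **A reader might infer that the same result could be declared a success or a failure.** The article sets no success rule, responder endpoint or decision threshold. The 12-month change is estimated in the same way under either figure; what differs is how its clinical relevance is described.
- **A reader might infer that a 1-point rule mostly counts noise and a 5-point rule does not.** That depends on an SD and an integer scoring that the article does not give. Assuming integer scoring, no true change and the implied SD of about 21.9, the chance of a gain is 1 − Φ(0.5/21.9) = 49% for at least 1 point and 1 − Φ(4.5/21.9) = 42% for at least 5. As responder cuts, the two would hardly differ.
- **A reader might infer that 5 is correct because it carries a citation.** The cited source is not available here, and the 5-point text lacks a direction just as the 1-point text does.

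**Conclusion.** The point holds as an unreconciled conflict in how clinical relevance of the primary outcome is defined. Any mean change from 1 to below 5 points is read in opposite ways by the two statements.

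The 25-fold sample-size ratio is the firm magnitude. It holds for any SD, alpha, sidedness or power, provided 150 is what a 5-point change requires, as the article says. The 12–15% power with 300 participants is conditional on the SD implied by n = 150, two-sided alpha 0.05, design power of 80–90% and no dropout.

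It is not shown which figure is right, nor that the power calculation itself is wrong. The estimate of the 12-month change is unaffected; its interpretation is not.

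**What to change.** Before the 12-month data are analysed, state one clinically relevant NEADL threshold, with its direction and level, in both Table 1 and the sample-size section. There are three ways to do so:

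- Align Table 1 with the 5 points that the power calculation uses.
- If 1 point is meant, keep it and restate what mean change the sample can detect. At the implied SD this is about 3.5 points with 300 participants.
- If one figure is an individual criterion and the other a group-mean criterion, say so, and label each.

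In every case, report the mean 12-month change with its 95% CI against the stated threshold.

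The cost is a line in Table 1 and a sentence in the sample-size section, carried into the SAP if it repeats either figure. If 5 points is kept, fewer results can be called clinically relevant. If 1 point is kept, the authors must accept that the study is not sized to detect it.
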